## Abstract

**Background:**

Personality Disorders that meet the criteria for a Severe Mental Illness (SMI-PD) tend to coincide with a greatly reduced quality of life and a lower life expectancy. Despite the numerous and complex needs of patients with SMI-PD, effective treatments for this group have not yet been established. Traditional treatments often fail to address the multitude of problems patients with SMI-PD struggle with and there is limited understanding about the treatment needs and effects. SMI-PD is associated with high economic costs to both the individual and society. Adaptive Mentalization-based Integrative Therapy (AMBIT) is a mentalization-based systematic approach designed to support teams in their care for people with multiple needs who distrust help. This study will investigate the effectiveness and cost-effectiveness of AMBIT in treating patients with SMI-PD.

**Methods:**

Patients aged 18 or older with SMI-PD receiving care at GGZ Rivierduinen and GGZ Altrecht (*n* = 160), mental health facilities in the Netherlands, will be recruited for this controlled naturalistic longitudinal cohort study. To assess treatment effectiveness and cost-effectiveness, self-report questionnaires will be administered and an electronic diary through the Experience Sampling Method will be used at three time points: at baseline (T0; start of treatment), and after 9 (T1) and 18 (T2) months of treatment. The questionnaires and diary will assess demographics, personality, social, and societal functioning, mentalizing capacity, epistemic mistrust, childhood trauma, attachment security, suicidality, and psychological resilience. A qualitative interview will be held at the end of treatment to evaluate treatment experiences. Additionally, therapists will complete questionnaires to evaluate the effectiveness of AMBIT. Data will be analysed using intention-to-treat multilevel regression analysis.

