### Design

2.1

This controlled, naturalistic, longitudinal cohort study will follow participants over 18 months of treatment to assess recovery outcomes in patients with SMI-PD across three settings: FACT, AMBIT-PD, and AMBIT informed-MBT. A naturalistic design was chosen to enhance ecological validity and generalizability, allowing treatment to reflect real-world practice rather than rigid protocols. Unlike a randomized controlled trial (RCT), which prioritizes internal validity, this approach better captures treatment effectiveness in complex, real-life settings where patient motivation—key to therapeutic success— will not be affected by randomization (40–43). Since participants must have already been in mental health care for at least two years (6–8), altering their current care for the sake of an RCT may be unethical and disruptive. The flexibility of the AMBIT approach, which focuses on restoring trust and adapting to individual needs, would also be compromised by a rigid study design, potentially increasing epistemic mistrust and disengagement (42). A naturalistic design minimizes exclusion due to strict criteria and reduces drop-out, leading to more complete data. However, the absence of randomization does increase the risk of bias from unknown confounders, which will be considered in the analysis (40, 42–44).

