### Participants

2.2

The study sample will consist of 160 patients with SMI-PD receiving care at GGZ Rivierduinen and GGZ Altrecht, mental health facilities in the Netherlands. 40 patients will be recruited at the FACT teams of Altrecht (FACT-ALT), 40 patients at the FACT teams of GGZ Rivierduinen (FACT-RIV), 40 patients at the AMBIT-PD teams of Altrecht (AMBIT-PD-ALT) and 40 patients at the AMBIT informed-MBT team of Rivierduinen (AMBIT-MBT-RIV). Participants will be recruited via their principal therapist in each of the participating teams when they meet inclusion criteria. Eligibility of each participant will be assessed before recruitment of a participant.

Participants are eligible if they 1) are 18 years of age or older, 2) are willing and able to give informed consent, 3) have a present diagnosis of a PD meeting DSM 5 criteria, 4) meet the criteria of SMI (5, 7, 8). This includes having a persistent psychiatric disorder that requires care and treatment, having undergone at least two years of treatment without achieving functional recovery (GAF ≤ 50), and experiencing impairment in social and/or societal functioning, such as difficulties in at least two areas of life, including financial issues, educational or occupational challenges, housing problems, relationship issues, substance abuse, or school/work difficulties. The dysfunction must be caused by or result in a psychiatric disorder, and coordinated care from professional caregivers in care networks is necessary to implement a treatment plan.

Participants are excluded from participation in this study if they 1) do not master the Dutch language, 2) are significantly under the influence of substances and are unwilling to detoxify elsewhere, or 3) if they have an intellectual impairment (IQ < 80, based on the Wechsler Adult Intelligence Scale).

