#### Feasibility

2.2.2

To map the feasibility of participant recruitment, we rely on the standard guideline of care for personality disorders (45). It is estimated that approximately 30% of the FACT teams meet the criteria for SMI-PD. GGZ Rivierduinen location Leiden has 4 FACT teams. Altrecht location Utrecht has 9 FACT teams. Each team has at least 200 clients in care on a yearly basis. Therefore, approximately 60 clients per FACT team are likely to meet the inclusion criteria of the study, which amounts to around 780 clients (45). As the study is observational in nature and only minimally burdensome for participants (questionnaires), and since we plan to provide a generous participation fee of 30 euros per measurement, we think it is reasonable to expect that around 10% of the clients will consent to participate. From previous naturalistic research (46), it was found that a vast majority (87%) of this target group was willing to participate in research. Rivierduinen has one AMBIT informed-MBT team, whereas Altrecht has five, who each treat 200 to 250 clients, nearly all of whom meet the inclusion criteria of the study, amounting to around 1000 likely eligible participants. Since this also concerns naturalistic research, we are confident that recruiting 80 participants at Rivierduinen and 80 at Altrecht is feasible.

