##### AMBIT-PD

2.5.1.2

The AMBIT- PD condition is provided in five teams at Altrecht. These teams are trained in the AMBIT methodology and focus on working in a mentalized manner with patients and aim at building a mentalizing network around the patients. These teams have daily multidisciplinary meetings and every two weeks either InterVision or supervision with the team. A major difference with the AMBIT informed MBT condition is that MBT group-therapy is not mandatory in the AMBIT-PD condition. In the AMBIT informed MBT condition, therapy is individualized, meaning that whether patients receive MBT group-therapy, individual MBT and other interventions, such as, family therapy, pharmacotherapy or trauma-therapy is adjusted to the patient’s needs and wishes. Patients in these teams are treated for, on average, three to five years, but sometimes longer.

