#### Multilevel (mixed) model analysis

3.1.3

Multilevel (mixed) model analysis will be conducted to compare outcomes for both conditions on the OQ-45.2, with baseline scores (T0), scores after 9 months (T1), and at the end of treatment after 18 months (T2) as dependent variables and treatment (FACT or AMBIT) as independent variable. The different levels for the multilevel (mixed) model analysis will be: 1) participant, 2) measurement wave, 3) outcome measure, and 4) location of sampling. A multilevel (mixed) model analysis uses all data and contributes to power in the analysis in contrast to case wise deletion for missing data.

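### T0 is defined as the start of treatment, but recruitment sets no limit on time already spent in the current team, so patients can enter at different points of treatment

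*Protocol article*

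**What the plan says.** **Time points.** The protocol article's Abstract (Methods) sets assessments "at baseline (T0; start of treatment), and after 9 (T1) and 18 (T2) months of treatment". Table 1 labels T1 and T2 by months of treatment. The primary model in section 3.1.3 uses scores "at the end of treatment after 18 months (T2"), and section 3.2 repeats that label.

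**Who is recruited.** Section 2.2: "The study sample will consist of 160 patients with SMI-PD receiving care at GGZ Rivierduinen and GGZ Altrecht", and "Participants will be recruited via their principal therapist in each of the participating teams when they meet inclusion criteria". The only eligibility rule on treatment time is a minimum, "having undergone at least two years of treatment without achieving functional recovery (GAF ≤ 50"). It refers to any earlier treatment, not to the current team. Section 2.1 rejects randomisation because "altering their current care for the sake of an RCT may be unethical and disruptive". Section 2.2.2 builds the FACT recruitment pool from "Each team has at least 200 clients in care on a yearly basis" and the AMBIT pool from the number of clients each team treats. Section 2.4 runs from recruitment through screening and consent to the T0 invitation without tying T0 to entry into the team.

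**Length of treatment.** Section 2.5.1.1 gives 18 months for MBT in the AMBIT informed-MBT team. For AMBIT-PD, section 2.5.1.2 says: "Patients in these teams are treated for, on average, three to five years, but sometimes longer". No duration is given for FACT.

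**The concern.** The primary comparison is the course of the OQ-45.2 from T0 to T2 under AMBIT and FACT. It is interpretable as the effect of a treatment over its first 18 months only if T0 is the start of that treatment for everyone. If patients can join part-way through, three things may follow:

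- Change before T0 is lost, and patients who left the team early are never enrolled.
- The non-recovery criterion, applied to an existing caseload, can also screen out patients who have already done well in that team.
- The propensity score in section 3.1.2 assumes characteristics measured before treatment. For someone already in the team, clinical measures taken at T0 are not pre-treatment, so matching on them could remove part of the effect under study.

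Prior exposure can also differ by setting, because the settings differ in length.

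**Working it through.** **1. The passages side by side**

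| Point | Reads as new starters | Reads as patients already in the team |
|---|---|---|
| T0 | Abstract: start of treatment | 2.4: follows consent, no link to team entry |
| T1, T2 | Table 1: months of treatment; 3.1.3: T2 ends treatment | 2.4: treatment continues after 18 months if needed |
| Population | 3.1.2: covariates described as pre-treatment | 2.1: current care left unaltered; 2.2: recruited by the patient's therapist in the team |
| Pool | – | 2.2.2: clients in care or being treated |
| Time in team | – | 2.2: no maximum and no entry window |

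The left column defines the measurement scale, and the right column defines who can enter. Following the right column as written does not guarantee the left.

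**2. The plan's own feasibility figure.** Inputs from section 2.2.2: 4 + 9 = 13 FACT teams, 200 clients each, 30% eligible.

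13 × 200 × 0.30 = 780, as stated. It is a count of clients in care, not of entrants.

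**3. What late entry does to the labels.** Let *a* be months already spent in the current team at T0. Exposure is then *a*, *a* + 9 and *a* + 18 months at T0, T1 and T2. In an 18-month course, 18 − *a* months remain at T0. Any *a* > 0 therefore puts the end of the course before T2. In AMBIT-PD, with an average of 36 to 60 months, T2 is generally not the end of treatment even when *a* = 0.

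**4. Illustration of *a*.** The document gives no distribution of time in team. Assume a steady caseload, a fixed treatment length *D* and even recruitment over the caseload. Then *a* is uniform on 0 to *D*, with mean *D*/2, and the share within the first 3 months is 3/*D*.

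| Setting | *D* (months) | Mean *a* (months) | Share in first 3 months |
|---|---|---|---|
| AMBIT informed-MBT | 18 | 18/2 = 9 | 3/18 = 17% |
| AMBIT-PD, lower average | 36 | 36/2 = 18 | 3/36 = 8% |
| AMBIT-PD, upper average | 60 | 60/2 = 30 | 3/60 = 5% |
| FACT | not given | not computable | not computable |

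If stays vary in length, the mean of *a* is E[T²]/(2E[T]), which is larger than E[T]/2. The table is therefore not an estimate for this trial.

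**5. Would new entrants suffice?** On the same steady-caseload assumption, with 200 clients per team:

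- AMBIT-PD: 5 × 200 = 1000 clients. 1000/5 = 200 to 1000/3 = 333 entrants a year.
- AMBIT informed-MBT: 200/1.5 = 133 entrants a year.

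Each arm needs 40. At 10% consent (the rate section 2.2.2 applies to FACT clients), AMBIT-PD would need 40/33.3 = 1.2 to 40/20 = 2 years, and AMBIT informed-MBT 40/13.3 = 3 years. At the 87% willingness cited there, even the MBT team would yield 0.87 × 133 = 116 a year.

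**The case against.** The strongest reply is that the only explicit definition of T0 is the start of treatment. Table 1 agrees, section 3.1.2 speaks of pre-treatment characteristics, and an 18-month MBT course fits an 18-month follow-up. Receiving care at the two institutions does not have to mean being in the study team already. A patient with two years of earlier treatment would be in care somewhere when newly entering a team, and the current-care argument in section 2.1 follows directly from that two-year rule. No passage says outright that patients part-way through treatment will be enrolled. This stands: if T0 really is team entry for everyone, the bias does not arise.

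It also stands that a condensed article need not list every covariate. The baseline data in section 2.3.2.1 and the confounders in section 3.1.2 are given as examples, so the absence of time in team from them does not show that it will be left out. Nor does a caseload count make recruitment of new entrants infeasible, as step 5 shows for the AMBIT arms.

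A reader might infer that the arms do start at different points, that the baseline does contain treatment effect, and that change is not comparable between arms. The document does not support that. It leaves these outcomes possible without establishing them.

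The reply does not remove the conflict. Sections 2.1, 2.2, 2.2.2 and 2.4 lean towards existing patients, and none of them makes the stated T0 true. The continuation note in section 2.4 qualifies the end-of-treatment label but does not correct it in section 3.1.3.

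**Conclusion.** The point holds as a conflict over what the baseline of the primary comparison is. T0 is defined as the start of treatment, while the recruitment rules as written allow entry at any point in a patient's time with the team. The baseline and the propensity covariates may then already reflect the team's effect, and prior exposure can differ between settings.

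Neither the size nor the direction of the bias can be determined from the document. The figures of 9 months and 1.5 to 2.5 years (18 to 30 months) rest on a steady caseload, fixed treatment length and even recruitment. They show what the text permits, not what will happen. This should be settled before analysis, because the meaning of the T0–T2 contrast depends on it.

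**What to change.** Reconcile the passages by stating whether T0 is entry into the team or enrolment in the study, and record the date of entry into the current FACT or AMBIT team for every participant. Then take one of two routes:

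- **Existing patients may enter.** Relabel T0, T1 and T2 as enrolment, +9 months and +18 months throughout, including Table 1 and sections 3.1.3 and 3.2. Put time in team in the propensity model and, by wave, in the OQ-45.2 model. Add a sensitivity analysis restricted to recent entrants.
- **Only new entrants are meant.** State the entry window in section 2.2, reword sections 2.1 and 2.2, and recount section 2.2.2 on new entrants. The end-of-treatment label for T2 still has to be squared with the AMBIT-PD durations.

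The first route costs one date per participant, text changes and slightly more analysis. The second would slow recruitment.

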**Discussion:**

Little is known about the treatment needs of patients with SMI-PD and the effectiveness and cost-effectiveness of an AMBIT approach on this group of patients. The results of the present study will therefore contribute to the development of more tailored and effective psychological treatment for this complex group of patients.

**Trial Registration:**

Research Portal of CCMO Onderzoek met mensen, Trial Registration Number NL-010303, https://www.onderzoekmetmensen.nl/en/trial/57877, registered on June 27, 2025. OSF Registries, https://doi.org/10.17605/OSF.IO/QHYCW, preregistered on May 7, 2025.

## Introduction

1

Much progress has been made in the treatment of personality disorders (PDs) (1–4), but less is known about what constitutes effective treatment for patients with PD who also meet the criteria for a severe mental illness (SMI). Delespaul and the Dutch Consensus group EPA (5) defined SMI-PD by the severity and complexity of symptoms, comorbidity - most commonly PTSD, depression, anxiety, and substance abuse -, and a history of therapeutic ruptures, in addition to meeting criteria of SMI, to distinguish them from PD and SMI (5–7).

Patients with SMI-PD experience problems pertaining to the ability to function in important areas of life, such as work, relationships, self-care and social activities (5–8). Moreover, these social problems tend to contribute to the persistence of PD symptoms. Consequently, because of the multitude of social and mental health problems, this group of patients reports a substantially reduced quality of life and lower life expectancy (6–8). Suicidality is an important cause of reduced life expectancy in patients with SMI and SMI-PD (9, 10). The combination of psychiatric distress, personal functioning difficulties, and interpersonal problems characterizing personality disorders, along with work, financial, and social challenges, complicates treatment for patients meeting SMI-PD criteria. Although SMI-PD affects a relatively small subset of patients, the associated high levels of healthcare utilization and occupational impairments can generate considerable economic strain on both individual and societal levels (11). Given the chronicity and multifaceted nature of SMI-PD, conventional mental healthcare systems frequently fail to adequately address the needs most commonly required by this group of patients and they frequently find themselves inadequately supported within the mental healthcare system (6–8, 12, 13).

Effective treatment for individuals with SMI-PD should address the social and interpersonal impairments that are often rooted in insecure attachment. Attachment is an innate survival mechanism, guiding infants to seek comfort from caregivers in times of distress and shaping their understanding of social environments (14, 15). Secure attachment relationships foster epistemic trust, which is the ability to recognize information from others as genuine and personally relevant. Epistemic trust enables social learning, allowing the individual to benefit from their social environment and to generalize this information to other contexts (14, 15). In contrast, insecure attachment, typically resulting from early adverse experiences, is associated with epistemic mistrust and impaired mentalizing, which impedes social learning. Patients with SMI-PD often struggle with epistemic trust due to adverse childhood experiences and attachment disruptions, leading to mistrust, poor communication, and social withdrawal; these interpersonal problems serve as maintaining factors for their mental health problems (6–8, 16–18). Evidence-based mono-therapies for PDs, such as dialectical behaviour therapy (DBT) (19), mentalization-based therapy (MBT) (20), schema therapy (ST) (21) and transference-focused therapy (TFP) (22), mainly focus on one aspect of personality pathology that patients with PD suffer from but do not comprehensively address the complex range of needs required by patients with SMI-PD. These treatments are often less effective due to the high levels of distress and complexity of problems in these patients. Furthermore, the involvement of multiple professionals across different domains (e.g., healthcare, legal, social services), which is often required in addition to treatment of personality pathology, frequently leads to fragmented or contradictory care, undermining trust and coordination and eventually the effectiveness of treatment.

SMI-PD patients are also often “hard to reach”, with only a small proportion seeking help. Those who do seek help may have had negative past experiences with caregivers or therapists who are often not fully equipped for the mentalization challenges that this group of patients poses, or face discouragement from other attachment figures, such as family members. As such, the patients’ history of trauma and insecure attachment may lead them to avoid or reject conventional treatment, responding with mistrust or hostility. This dynamic challenges therapists who may themselves struggle to maintain mentalization and emotional resilience, increasing the risk of therapeutic rupture. When such therapeutic rupture happens, the therapeutic relationship suffers, which reinforces patients’ mistrust in the mental health system (6, 23–28).

The mental health care costs for patients with SMI-PD are in general high as a result of the severity and pervasiveness of their mental health problems, and failure to recover from conventional treatment due to their attachment problems leading to repeated rejection of help (11, 13, 29). Besides a health-related burden, the individual patient with SMI-PD can accrue significant economic strain, debt, and liability, which can also affect their immediate family and society. These costs consist of direct healthcare costs (i.e. increased stress, or poor lifestyle choices) and of non-healthcare costs such as reduced productivity due to illness or limited societal participation (4, 30, 31). Cost-effectiveness is therefore, together with effectiveness, an important consideration in the choice of treatment. Health economic evaluations can contribute to decision making on how to optimally allocate (scarce) health care resources.

In the Netherlands, patients with SMI-PD tend to be treated in Flexible Assertive Community Treatment (FACT) teams, which are designed to provide community-based care for individuals with SMI. FACT teams employ a flexible switching system that combines care for two patient groups requiring different intensities of support. For clients needing lower-intensity care, individual case management is provided and integrated with multidisciplinary treatment and support. In crisis situations, intensity of care can be escalated, and a shared caseload approach is adopted to ensure outreach, persistent support, and continuity of treatment. The flexibility in switching between the two types of care aims to enhance continuity of care and reduce treatment drop-out (32). Although FACT has been proven effective for patients with SMI, the focus on psychosis as primary patient group limits its applicability for patients with SMI-PD. FACT teams may have less experience addressing the complex needs of patients with PDs, including difficulties related to (counter)transference in the therapeutic relationship, pre-mentalizing modes, and trauma-related symptoms. Consequently, treatment dropout of patients with SMI-PD is rarely attributable solely to intrapsychic, motivational problems; rather, dropout often reflects the patients’ perspective of epistemic mistrust stemming from attachment problems or the inability of conventional care models, such as FACT, to adequately address the full range of potential limitations and challenges associated with SMI-PD (7).

Adaptive Mentalisation-based Integrative Therapy (AMBIT) is a mentalization-based systematic framework that was originally designed to support teams involved in care for young people with multiple needs who are reluctant to trust help (17, 33–35). AMBIT is based on the concept that epistemic mistrust is an undermining factor in the effectiveness of care and treatment, and aims to restore epistemic trust between the individual and their helping network to enable new social learning (18, 33, 34). AMBIT is characterized by adaptability in response to an individual’s needs and that of the systems involved in care around the individual, and to what is perceived as helpful, with a special emphasis on promoting mentalizing skills. Mentalizing is the mental process that allows individuals to interpret and understand the mental states of themselves and others, which underlie overt behaviour (17, 35, 36). AMBIT uses mentalizing as the unifying framework across four domains: in 1) face-to-face interactions with individuals, 2) through structured, team-based mentalizing-enhancing sessions that focus on establishing effective relationships within teams and 3) on collaborating within multi-agency networks and family to care for them, 4) eventually fostering a learning culture. The focus on integrated care and collaboration in a coordinated network around the patient, overlaps with FACT. However, AMBIT differs from FACT, in that AMBIT uses mentalization as its framework and addresses distrust, relational repair, engagement, and adaptability, which eventually restores epistemic trust enabling new social learning. These factors seem to be primary mechanisms of change in AMBIT informed teams and are thought to contribute to the positive and the long-term effectiveness of this approach (33, 37), distinguishing AMBIT from the typical way care for patients with SMI-PD is currently organized such as FACT (6–8). It is suggested that AMBIT facilitates ‘fortuitous events’ by focusing on enabling the helping system surrounding a patient to act in a more understanding (more mentalized) and less conflicted manner. This approach reduces incongruency in the simultaneous support provided to a patient and contributes to the ‘extra-therapeutic change’, ultimately enhancing effectiveness of AMBIT. Findings suggest a generally positive impact of AMBIT-informed teams on symptom reduction and improvements in functioning among individuals with multiple problems (33, 34).

When possible, AMBIT includes evidence-based therapies but also emphasizes practice-based evidence, focusing on what works for the teams involved in supporting the individual. It includes multiple interventions tailored to the specific needs of each individual, which may involve proactive facilitation of access to (and use of) help provided by other agencies (e.g. housing, financial support, courts, education or training, employment support, etc.). These agencies may struggle to engage SMI-PD patients without a “team around” approach, in which a dedicated worker actively mentalizes both their professional predicaments and the patients’ perspective. Such interventions may focus on trauma (e.g., Narrative Exposure Therapy, Eye-Movement Desensitization Reprocessing), family dynamics (systemic therapy or relational therapy), or educational/vocational difficulties (individual placement and support). Mentalization Based Therapy (MBT), an evidence-based psychotherapy for borderline personality disorder (BPD) targeting mentalizing deficits, is typically included for personality difficulties in an AMBIT approach, at least on an individual basis. MBT has demonstrated significant reductions in hospitalization, self-harm, and in improvements in social and interpersonal functioning, with long-lasting benefits (36, 38). Its focus on enhancing mentalizing capacity makes MBT highly likely to be an important component of care for individuals with SMI-PD, making AMBIT particularly suitable for this patient group.

Considering the potential positive impact of AMBIT informed teams on reducing symptoms and improving overall functioning in individuals with multiple problems (33, 39), it is anticipated that this approach reduces epistemic mistrust resulting in more positive experiences in daily life, ultimately breaking the cycle of the persistence of problems. These improvements may also contribute to a reduction in healthcare costs and non-healthcare costs, such as loss of earnings and financial burden because of, amongst others, fewer hospital admissions, fewer crisis contacts, fewer general health costs, reduced time demands on mental health workers, and diminished productivity loss for relatives. A comparative health-economic evaluation is needed to assess whether the AMBIT approach is more cost-effective than FACT.

This study aims to investigate the effectiveness of an AMBIT approach in treatment and care for patients with SMI-PD.

The primary objective of this study is to investigate the effectiveness of AMBIT for patients with SMI-PD in comparison to treatment with FACT. It is hypothesized that an AMBIT approach will be more effective in improving outcomes on a broad spectrum of life domains (e.g. leisure activities, education, housing, family, symptoms, and drug use) in patients with SMI-PD than FACT.

Furthermore, this study aims to investigate differences in treatment effects of the following secondary variables regarding personality functioning, and social- and societal functioning, mentalizing capacity, epistemic trust, and suicidality. It is hypothesized that patients in the AMBIT condition show greater improvement on a broad spectrum of outcomes, considering psychiatric symptoms, social ecology, relationship networks/qualities, and resiliencies as measured by the instruments included in the present study as discussed in the method section.

Cost-effectiveness will also be evaluated for AMBIT. It is hypothesized that AMBIT will be a more cost-effective treatment than FACT.

Lastly this study aims to investigate variables that may moderate and mediate treatment outcome. It is expected that severity of childhood trauma, and duration of illness have a moderating effect on treatment outcome, while epistemic trust and mentalizing capacity are expected to have a mediating effect on treatment outcome.

